### Procedures

Participants will attend a research clinic as close to home as possible. The clinics will last approximately 3 hours. During the research clinics, participants will be guided through five stations, which are outlined in figure 3.

**Figure 3 F3:**
[figure not shown]
Flow chart of research clinic activity. 2D, two-dimensional; 3D, three-dimensional; CD-RISC-10, Connor-Davidson Resilience Scale-10; CLEFT-Q, Cleft Questionnaire; CPITN, Community Periodontal Index for Treatment Needs; DMFT, Decayed, Missing, Filled Teeth Index; GAD-7, Generalised Anxiety Disorder-7; HLS-Q12, Health Literacy Survey-Q12; IMI, Institute of Medical Illustrators; LOT-R, Revised Life Orientation Test; ModRUM, MODular Resource-Use Measure; OHIP-14, Oral Health Impact Profile-14; PHQ-8, Patient Health Questionnaire-8; PROMIS, Patient-Reported Outcome Measurement Information System; SF-36, Short Form 36; WPAI, Work Productivity and Activity Impairment questionnaire.

### Data collection methods

Data will be collected through self-report questionnaires, photographic images, hearing and speech assessments and a dental examination (including an intraoral scan). The research clinic will be facilitated by a member of the Cleft@18–23 team with support from an administrative personnel member from the local site team. All data collected from the research clinics are summarised in table 1.

**Table 1 T1:** Summary of research clinic stations and data collection

Research clinic station	Measures	Onsite activity for data collection
1. Self-report questionnaire—part 1	Demographics including EDI characteristics	Self-report
	Satisfaction with appearance and function	CLEFT-Q
	Health-related quality of life (emotional role subscale) (*PRIMARY OUTCOME MEASURE*)	SF-36
	Depression	PHQ-8
	Anxiety	GAD-7
	Health literacy	HLS-Q12
	Resilience	CD-RISC-10
2. Medical photography	Nasolabial appearance/teeth appearance	2D photographs
	Facial shape and symmetry	3D images
3. Hearing and speech assessment	Hearing	Pure tone audiometry
	Speech	Audio-visual recording of a speech sample
4. Dental examination	Dental arch alignment	Intraoral scans
	Oral health—dental	DMFT
	Oral health—periodontal	CPITN and OHI-S
5. Self-report questionnaire—part 2	Satisfaction with oral health	OHIP-14
	Access to treatment	Dental access self-report
	Orthodontic treatment	Orthodontic treatment self-report
	Productivity loss	WPAI
	Resource use	ModRUM
	Use of private healthcare	Private healthcare use self-report
	Out-of-pocket expenses	Out-of-pocket expenses self-report
	Social functioning	Harter self-perception profile
	World view	LOT-R
	Global health-related quality of life	PROMIS

CD-RISC-10, Connor-Davidson Resilience Scale-10; CLEFT-Q, Cleft Questionnaire; CPITN, Community Periodontal Index for Treatment Needs; 2D, two-dimensional; 3D, three-dimensional; DMFT, Decayed, Missing, Filled Teeth Index; EDI, Equality, Diversity and Inclusion; GAD-7, Generalised Anxiety Disorder-7; HLS-Q12, Health Literacy Survey-Q12; LOT-R, Revised Life Orientation Test; ModRUM, MODular Resource-Use Measure; OHIP-14, Oral Health Impact Profile-14; OHI-S, Oral Hygiene Index-Simplified; PHQ-8, Patient Health Questionnaire-8; PROMIS, Patient Reported Outcome Measurement Information System; SF-36, Short Form 36; WPAI, Work Productivity and Activity Impairment questionnaire.

#### Self-report questionnaires

The self-report questionnaires omprise questions relating to demographics and experience along with measures from validated patient questionnaires, which are discussed further under the ‘Derived variables’ section. The self-report questionnaire will be presented electronically through Research Electronic Data Capture (a secure web application for building and managing online surveys and database: https://project-redcap.org) and Concerto (an adaptive testing platform developed and maintained by the University of Cambridge Psychometrics Centre: https://concertoplatform.com). The self-report questionnaire will be broken down into two parts: the first part of the questionnaire to be completed at the beginning of the research clinic and the second part towards the end of the research clinic. This is based on input from PPI to split the questionnaire into two parts for participants’ ease. If a participant has learning difficulties, a friend, carer, parent or member of the study team will be able to help read the questions and record their responses. A summary of the measures used in each section of the self-report questionnaires is provided in table 1. The first part of the questionnaire will also collect data on general demographics including age (in years), sex at birth, gender, ethnicity, parental employment (as an indicator of socioeconomic status), cleft subtype, syndromic status and cleft surgical history (number and type of operations), which will be used as the exposures/confounders/effect modifiers in statistical analysis. In the second part of the questionnaire, further questions will collect data on access to dental care and experience of orthodontic treatment; these have been developed by the cleft specialist dentists and orthodontists in the UK. Following recommendations from our co-applicants and PPI group, the end of each part of the self-report questionnaire concludes with optional questions, which focus on how having a cleft may have had a positive impact on participants. This section will comprise a series of statements that the participant can opt to complete:

Advice I would give my younger self…I’m proud of myself because…Something I want people to know about me is…

#### Medical photography

A medical photographer will take 2D and 3D images, following the Institute of Medical Illustrators guidelines.^10^ Both core and optional 2D views will be captured. These include extraoral (lateral, anterior-posterior views of the face and the lip and nose areas) and intraoral views (buccal teeth, palate, occlusal mirror, teeth mirror, teeth overjet and alveolus). The Vectra H2 3D camera will capture 3D views from three angles: 45° left, front and 45° right of the face.

#### Hearing

Hearing levels will be screened by the speech and language therapist facilitating the research clinic using the hearScreen from hearX.^11^ This provides a reading for each ear across a range of frequencies using calibrated over-ear headphones and secure software via a Samsung Galaxy smartphone. It takes 5–10 min and has been validated for use outside of audio booths.^12^ Participants will be instructed by the speech and language therapist to place the headphones over their ears. The speech and language therapist will play tones via the smartphone at a 35 dB level. The participant will indicate when they have heard a tone by raising their hand and the speech and language therapist will record this via the smartphone.

#### Speech

A standardised speech sample will be collected using high-quality audio and video recordings in a quiet room with the subject facing natural light if possible. Each participant will sit in front of a pale neutral background. The face and upper neck will be framed in the picture. The sample will follow the protocol used in the Great Ormond Street Speech Assessment (GOS.SP.ASS)^13^ and includes the following:

Conversational speech.Rote speech including counting from 1 to 20 and 60 to 70.Reciting the days of the week.Repetition of the 16 GOS.SP.ASS sentences.A picture description task for connected speech and language sample.

#### Dental examination

The study dental therapist/hygienist will carry out the dental examination. They will check for decayed, missing and filled teeth and carry out a periodontal examination. A digital impression for dental arch alignment will be made using the Dentsply Sirona Primescan two digital intraoral scanner, which will be used to take occlusal, buccal, lingual, approximal and full jaw scans. Bite is also captured. The scanner will be used, cleaned and disinfected, in accordance with the guidance provided by the manufacturer (Dentsply Primescan Connect Operating Instructions, available from https://www.dentsplysirona.com/en-gb/discover/discover-by-brand/primescan.html). The digital scans will be captured on a study laptop used specifically for the collection of intraoral scans.

### Derived variables

#### Primary outcome measure

The variable used as the primary outcome measure for this study will be derived from the SF-36.^14^ We will use the five questions of the emotional role subscale of SF-36, also known as Mental Health Inventory. SF-36 was chosen to derive the primary outcome measure following the focus groups held with young adults born with CL/P,^6^ during which it was established that emotional well-being was the primary concern while transitioning into adult care.

The Patient-Reported Outcome Measurement Information System (PROMIS)^15^ Global Health Scale will also be included. This is a standardised psychometric instrument containing 10 questions pertaining to health-related quality of life. The SF-36 emotional role subscale will remain as the primary outcome measure due to its use in calculating the power of the study and for comparison with older literature.

The decision to retain both the SF-36 and the PROMIS, which has been designed to supersede the SF-36, was driven by the desire to compare the results from this study with other studies, which were carried out prior to the development of the PROMIS and which therefore used the SF-36. However, we also want to enable future researchers to compare their results using the PROMIS with our data and using only the SF-36 would limit that ability. In order to reduce repetition within this part of the questionnaire, we limited the questions from the SF-36 to just those five which comprise the emotional role subscale, as the study was designed with these forming the primary outcome measure and the means for calculating the sample size needed to ensure a robustly powered study.

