UK cleft teams have acknowledged that variation exists in services and have suggested that outcomes for young adults born with CL/P at transition may differ between subpopulations, including those identified by equality, diversity and inclusion characteristics. Specifically, concerns about variation due to geography, ethnicity and socioeconomic status were raised. The focus group with young adults born with CL/P identified concerns that young men were less likely to access support than young women.

The Cleft@18–23 study therefore aims to be the first to investigate outcomes for young people born with CL/P after completion of routine care and explore and explain any observed variation. It will also seek to develop a tool to help all young people navigate the transition of care and access ongoing treatment and support as adults where necessary. The study programme will achieve this through four work packages. The first of these work packages (WP1) is the Cleft@18–23 research clinics. The focus of this work package is to collect data on outcomes at the end of routine care and to explore variations across regions, socioeconomic status, ethnicity, gender and biological sex. The protocol for WP1 is presented in this paper.

The WP1 protocol has been developed with input from a series of focus groups with each of the core disciplines involved in cleft care (speech and language therapists, audiologists, dentists including specialist orthodontists and restorative dentists, clinical psychologists, cleft nurse specialists and surgeons) and two focus groups with young people aged 16–20 years born with a CL/P. The protocol was further refined with input from all 16 regional centres following visits to each centre by the Chief Investigator, and by patient and public involvement (PPI) partners in this programme of work.

This study aims to answer the following primary research question: what are the levels of emotional well-being in young adults aged 18–23 years born with a CL/P and do these vary across ethnicity, biological sex, socioeconomic status and geographic location?

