### Power calculations

A sample of 600 would allow a mean score of 86.4 to be estimated with a 95% CI of 84.2 to 88.6 (mean and SD based on Foo *et al*^8^) for the primary outcome measure (the emotional role subscale of Short Form 36 (SF-36)). With just over 1000 babies born each year with CL/P, the total population available to recruit from over a 2-year period is approximately 7000 (1000 individuals born with cleft each year for ages 18–23—totalling 6000—plus an additional year of recruitment to include young adults who turn 18 during the first year of recruitment). The recruitment rate for a comparable study run by the same team and involving younger children was 75%^9^; therefore, recruiting 600 is achievable. Nevertheless, we propose to over-recruit by 40 (total sample size 640) as contingency for missing data.

To achieve a sample size of 640, we aim to recruit from across the UK’s cleft teams. Some serve a larger population than others, so it is likely that we may recruit more from some sites than others. Our work with young people to date suggests that they would be willing to attend this research clinic. We aim to recruit participants across all groups to ensure that the study sample reflects the general population in terms of ethnicity, socioeconomic status, gender and cleft subtypes. Recruitment will be facilitated through targeted dissemination of study information via general medical practices, dental practices and community organisations serving diverse ethnic groups. Regular evaluation of those recruited will ensure the sample is representative of target population in ethnicity, biological sex, socioeconomic status and geographic location to minimise the risk of selection bias.

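### The primary outcome is given the names of two separately scored SF-36 scales, and the planning mean and confidence interval are attached to the one that the item count does not fit

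*Protocol article*

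**What the plan says.** The primary research question at the end of the Introduction asks "what are the levels of emotional well-being in young adults aged" 18 to 23 years, and whether those levels vary across ethnicity, sex, socioeconomic status and location.

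Under Primary outcome measure, the outcome is given two names and an item count: "We will use the five questions of the emotional role subscale of SF-36, also known as Mental Health Inventory". The same section says that nothing else from the instrument is administered: "we limited the questions from the SF-36 to just those five which comprise the emotional role subscale". It also says why the outcome is kept alongside PROMIS: "The SF-36 emotional role subscale will remain as the primary outcome measure due to its use in calculating the power of the study", with comparison against older literature as the second reason.

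Two other places use the first name only. Table 1, under Data collection methods, labels the primary outcome "Health-related quality of life (emotional role subscale". Power calculations states "A sample of 600 would allow a mean score of 86.4 to be estimated with a 95% CI of 84.2 to 88.6" and says that this is "for the primary outcome measure (the emotional role subscale of Short Form 36 (SF-36". The SD is not printed; the text says only "mean and SD based on" a cited study.

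**The concern.** The two names do not belong to one scale. By the structure of the SF-36, role limitation due to emotional problems is a three-item scale on how far emotional problems restrict work and daily activities. The Mental Health scale (the five-item Mental Health Inventory) asks about mood. They are scored separately, and an emotional role subscale with five questions does not exist.

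So the definition contradicts itself, and no other section resolves it. Three things are at stake.

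- **Which score is the primary outcome.** A coarse role-limitation score and a graded mood score differ in meaning and distribution. Data analyses chooses the regression model by outcome type, so the choice also bears on the model.
- **Whether the planning figures apply.** If the five mood items are collected but the mean and SD come from the role scale, the expected mean and interval describe a different score.
- **Whether the stated reasons for the outcome hold.** Its use in the sample-size calculation and its comparability with older studies both require that the scale collected is the scale those sources used.

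**Working it through.** **1. What each section points to**

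| Place | What it states | Scale it points to |
|---|---|---|
| Introduction, primary question | emotional well-being | Mental Health (five items) |
| Primary outcome measure | five questions | Mental Health (five items) |
| Primary outcome measure | Mental Health Inventory | Mental Health (five items) |
| Primary outcome measure | emotional role subscale | Role-emotional |
| Table 1 | emotional role subscale | Role-emotional |
| Power calculations | emotional role subscale, mean 86.4 | Role-emotional |

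The separation of the two scales is general knowledge of the instrument; the article does not state it.

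**2. The plan's own figure**

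Inputs from Power calculations: n = 600, mean 86.4, 95% CI 84.2 to 88.6.

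- Half-width = (88.6 − 84.2)/2 = 2.2. The interval is symmetric about 86.4.
- Half-width = 1.96 × SD/√n, so SD = 2.2 × √600/1.96 = 27.5.
- Allowing for rounding of the half-width (2.15 to 2.25), SD lies between 26.9 and 28.1.
- Putting 27.5 back: 1.96 × 27.5/√600 = 2.20.

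The figures are coherent. Because the SD is not printed, this is back-solving and not an independent reproduction.

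**3. What kind of score has these moments**

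Assumption: scoring on 0-100, which the article does not state.

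- Largest possible SD at mean 86.4 = √(86.4 × 13.6) = 34.3.
- Ratio: 27.5/34.3 = 0.80.
- Distance from mean to ceiling: (100 − 86.4)/27.5 = 0.49 SD.

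An SD this close to its maximum, with the ceiling half an SD away, is what a coarse, nearly all-or-none score produces. It would be unusual for a graded mood score.

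**4. How far that inference carries**

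I found by linear programming the smallest and largest share of people at exactly 100 that fit mean 86.4 and SD 27.5 on different score grids.

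| Grid (assumed) | Share at 100 |
|---|---|
| 0/33/67/100 | 74% to 80% |
| 13 levels | 36% to 80% |
| Steps of 5 (21 levels) | 3% to 80% |
| Steps of 4 | 0% to 80% |

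Only the four-level grid forces a heavy ceiling, and that grid presupposes role-scale scoring. The finer grids can carry the same mean and SD. The moments are therefore suggestive, not decisive.

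**5. Effect on precision**

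The article gives no SD for the other scale, so the SDs below are assumptions. Half-width at n = 600 is 1.96 × SD/√600:

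| SD | Half-width |
|---|---|
| 15 | 1.20 |
| 17 | 1.36 |
| 20 | 1.60 |
| 25 | 2.00 |
| 27.5 (implied) | 2.20 |
| 30 | 2.40 |

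With an SD of 17 to 20 the half-width is 1.4 to 1.6, tighter than the stated 2.2.

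**The case against.** The strongest reply is that one label is wrong and nothing more. The outcome section says five items twice and says that the same items were the basis for the sample size. The second name, the focus-group rationale and the research question all agree with them. On that reading, emotional role is a misnomer, and the planning mean and SD may well be those of the five-item scale. The cited study is not at hand, so this cannot be excluded. Item wording and scoring also commonly sit in a fuller protocol or in the questionnaire, and their absence from an article is no fault.

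Much of this stands. It rules out two stronger readings that a reader might infer.

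- **That the sample size was computed for the wrong scale.** The distributional pattern only suggests it, because finer score grids allow the same mean and SD and the source is unseen. Nor would it make 600 too small: under the assumed SD of 17 to 20, precision improves.
- **That the form carries the wrong items, so the primary outcome cannot be scored.** The questionnaire is not shown, and nothing in the text says which five items are on it.

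The objection does not remove the contradiction. The point is not missing detail: the article states that two different scales are one, and its sample-size section and Table 1 carry only the name that its item count does not fit. A reader cannot tell from the article which score will be reported or which published values are comparable.

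**Conclusion.** The point holds as a wrong definition of the primary outcome. The text equates two separately scored SF-36 scales. Item count, second name and research question favour the five-item Mental Health scale; the planning mean and the Table 1 label go to the emotional role subscale.

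That the planning figures come from the role scale is a plausible inference. It rests on an implied SD of 27.5, on 0-100 scoring, and on the judgement that an SD at 80% of its maximum is unusual for a graded score. It is not established.

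The cost is an ambiguous primary outcome, an expected mean and interval that may not apply to it, and a risk of comparison with the wrong published values. No loss of precision and no loss of data is shown. The check is nevertheless pressing: recruitment began in April 2025, clinics are scheduled from June 2025 to May 2027, and only five SF-36 items are collected.

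**What to change.** 1. Check which five items are on the questionnaire and confirm that they belong to the intended scale.
2. Use one scale name, with its items and score range, in Power calculations, Table 1 and Primary outcome measure. If the mood items are the intended outcome, remove the emotional role label; if the role scale is intended, remove the Mental Health Inventory name and correct the item count.
3. Check in the cited study that the mean of 86.4 and its SD are for that scale. Print the SD. If they are for the other scale, restate the expected mean and confidence interval.
4. Limit comparisons with older literature to results on the same scale.
5. If the items on the form are not those of the intended scale, amend the questionnaire promptly, since no other SF-36 items are collected from which the score could be recovered.

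The cost is a wording correction and at most one recalculated interval if the form carries the intended items, and a questionnaire amendment if it does not. Nothing here calls for more participants.

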#### Secondary outcome measures

There are multiple secondary outcome measures for this study covering the domains of patient satisfaction, aspects of psychosocial well-being, facial appearance, hearing and speech, dental outcomes and oral health, growth, access to care and the economic impact of a cleft diagnosis for patients. The derived variables for these are outlined below.

##### Satisfaction with appearance and function

The Cleft Questionnaire^16^ is a standardised patient-reported outcome measure specific to the CL/P population suitable for use with people aged 8–29 years. Variables reflecting patient satisfaction with the following will be derived:

Appearance of the faceAppearance of the lipsAppearance of the noseAppearance of the nostrilsAppearance of the jawsAppearance of the teethAppearance of the cleft lip scarPsychological functionSocial functionSpeech distressSpeech functionEating and drinking

Additional variables regarding patient satisfaction with oral health will be collected using the Oral Health Impact Profile-14. This is a 14-item questionnaire used to measure participants’ satisfaction with their teeth, mouth or dentures.^17^ This will allow comparisons with normative data from the general population.

##### Psychosocial well-being

Variables pertaining to the presence and severity of depression and anxiety will be derived from the Patient Health Questionnaire-8^18^ and the Generalised Anxiety Disorder-7.^19^ A variable measuring participants’ sociability and relationships will be derived from the Harter Self-Perception profile.^20^ A variable measuring resilience in stressful situations will be derived from the Connor-Davidson Resilience Scale-10 (CD-RISC-10), a 10-item scale derived from the 25-item CD-RISC-25, will be used to measure ability to cope with stressful life situations.^21^

